#### Recruitment and data collection

Patient recruitment in ETHER started in October 2019 and ended in February 2021. The principal investigator was responsible for recruiting the intervention group (i.e., participating in the TPE programme) in a CSAPA in Avignon. Four different sessions of the 10-week TPE programme enabled us to enrol a total of 34 (i.e. four more than expected) patients in the intervention group. At the beginning of a programme session, all participants were presented ETHER study and proposed to participate. Those who accepted signed the informed consent and were enrolled. The control group comprised 58 (i.e. two less than expected) patients enrolled in three sites with the support of medical staff: 30 were recruited in two CSAPA in Digne-les-Bains and in Avignon (the same CSAPA as for the intervention group but in a different service), and 30 more in an inpatient private clinic in Marseille (Fig. 2). People attending those two CSAPAs and the clinic and eligible to participate were identified by the local staff and then proposed to participate in the study during a medical or psychosocial visit. Those who accepted signed the informed consent and were enrolled. In the private clinic, participants were hospitalized for 5 weeks, and underwent a medically-supervised withdrawal. Pharmacological treatments were dispensed according to their individual needs, and participants benefited from a multidisciplinary follow-up. After the hospitalization, participants were followed-up as outpatients at the same clinic, were referred to another addictology service (such as a CSAPA), or to their general practitioner according to their geographical constraints. In both CSAPAs, the ‘treatment as usual’ consisted in tailored and patient-centred care plans. According to participant’s history, needs and demands, they regularly came to the centres to benefit from social and psychosocial follow-up and participate in individual and/or group activities. Pharmacological treatments were dispensed according to their individual needs and therapeutic objectives.

**Fig. 2 Fig2:**
[figure not shown]
ETHER: general study design. Abbreviations: TPE: Therapeutic patient education

Participants in both groups (i.e. intervention and control) were assessed at study enrolment (M0) and again 6 months later (M6) (i.e., 14 weeks after they end the Choizitaconso programme), using both a CATI and individual face-to-face interview (Fig. 3).

**Fig. 3 Fig3:**
[figure not shown]
Participant timeline

Anxiety and depressive symptoms, alcohol-related neuropsychological impairments and capabilities were assessed in the face-to-face interview. In the CATI interview, data on the primary outcome and other secondary outcomes were collected as were sociodemographic and medical data (Table 2). Alcohol consumption was measured using a short form of the Alcohol Use Disorder Identification Test (AUDIT-C) [40].

#### Sample size calculation

The CSAPA delivering the intervention could not enrol more than 25–30 persons per year. Accordingly, in order to avoid overly prolonging the study and to ensure adequate power, we decided to include twice as many controls than intervention participants. As there are no comparative estimates in the literature to predict the natural variation in the number of alcohol-related harms over follow-up after a TPE intervention, the sample size was computed according to the following assumptions: (1) the Choizitaconso TPE programme will be considered effective if it results in a reduction of at least 30% in the number of alcohol-related harms in the intervention group vs. an expected 5% reduction in the control group over a 6-month period. With an alpha = 0.05 and a power of 80%, we estimated we would need 30 individuals in the intervention group and 60 in the control group to be able to demonstrate a significant difference between both groups.

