#### Controlled intervention study outcomes

##### Principal outcome

The controlled intervention study comprises a 34-item ad-hoc questionnaire administered through a Computer-Assisted Telephone Interview (CATI). The items relate to 34 different psychosocial, behavioural and physical harms. They were chosen according to a Delphi approach as follows: first, a list of possible questions were identified by the study’s researchers in the international literature from existing and validated questionnaires; second, during several working sessions, peer educators (former people with AUD), approved or adapted those questions from the list which they felt would guarantee the relevance of the study outcomes. Collaboration between the peer educators and the research team followed the guidelines set down for community-based participatory research [38].

The 34 alcohol-related harms are measured as dichotomous (yes/no) variables. The controlled intervention study’s primary outcome is the number of alcohol-related harms experienced (ranging between 0 and 34). This number provides a measure of the ‘harm burden’ of alcohol use. Alcohol-related harms are assessed at enrolment for the intervention group (i.e., before the study participant commences the Choizitaconso TPE) and 6 months later (i.e., 14 weeks after the end of the programme).

For further information on the different alcohol-related harms, see Table 1 below.

**Table 1 Tab1:** List of the community-validated alcohol-related harms (primary outcome)

1. Professional neglect
2. Neglecting parental responsibilities
3. Neglecting conjugal responsibilities
4. Damaging a close friendship
5. Damaging an intimate relationship
6. Damaging a family relationship
7. Impulsiveness—saying or doing something you regret afterwards
8. Driving under the influence of psychoactive substances, drugs, alcohol
9. Problems with the legal system
10. Difficulties falling asleep
11. Difficulties staying asleep
12. Waking early
13. Hot flashes and/or night sweats
14. Hangover, vomiting, being sick after drinking
15. Alcohol-related physical injury
16. Trembling hands
17. Blackouts/memory problems
18. Neglecting own health in general
19. Neglecting physical appearance
20. Neglecting hygiene
21. Taking risks (crossing the street without first looking, fighting, having unprotected sexual intercourse, etc.)
22. Not eating regularly
23. Skipping meals
24. Increased drug consumption (cannabis, cocaine, anxiolytics, etc.)

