#### Data analysis plan

The planned data analyses will be organized in several steps as follows:(A)Descriptive analyses: sociodemographic data and alcohol consumption levels will be compared across study sites and between both the intervention and control groups at enrolment, using parametric and non-parametric tests.(B)Comparison between enrolment (M0) and 6 months (M6) of the percentage variation in the number of alcohol-related harms, using a binomial test.(C)Modelling of variation in the number of alcohol-related harms using linear regression, to determine whether any differences between groups persists after adjustment for possible confounders (identified in step A) or other predictors.(D)Repeat analysis B and C for secondary outcomes using linear regression models.(E)Post-study analysis: factor analysis to aggregate the alcohol-related harms measured at enrolment, in order to identify one or two main alcohol-related harm dimensions, and verify to what extent the intervention is effective for these dimensions.

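### The stated 80% power for 30/60 is unsupported for the count of harms: the figures fit a comparison of two proportions, and step B of the analysis repeats the mismatch

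*Protocol article*

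**What the plan says.** Under Principal outcome, the study's "primary outcome is the number of alcohol-related harms experienced (ranging between 0 and 34"): 34 yes/no items summed for each person, measured at enrolment (M0) and six months later (M6).

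The Sample size calculation assumes a "reduction of at least 30% in the number of alcohol-related harms in the intervention group vs. an expected 5% reduction in the control group". On allocation it says "we decided to include twice as many controls than intervention participants", because the site delivering the programme could take only 25–30 people a year. It then concludes: "With an alpha = 0.05 and a power of 80%, we estimated we would need 30 individuals in the intervention group and 60" controls, "to be able to demonstrate a significant difference between both groups". The section names no test, sidedness, baseline mean or SD. It says there are no comparative estimates in the literature from which to predict the natural variation in the outcome.

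The Data analysis plan has two steps for this outcome. Step B applies a binomial test to the percentage variation in the number of harms between M0 and M6. Step C is "Modelling of variation in the number of alcohol-related harms using linear regression", to see whether a group difference survives adjustment. Recruitment and data collection reports 34 intervention and 58 control participants enrolled.

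**The concern.** A percentage fall in a count and a percentage of people with an event are different quantities. For an event, the variance follows from the proportion itself, p(1−p), so two proportions, alpha, power and the allocation ratio are enough to fix a sample size. For a change in a count, the variance is a separate quantity that must be supplied. The article supplies none, yet arrives at a definite 30 and 60.

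If the 30% and 5% were entered as proportions of participants, the 80% describes a responder comparison. The article defines no responder endpoint, such as the share of people reaching a set reduction. The same question arises in step B, because a binomial test needs a yes/no result per person and a percentage change in a count is not one.

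At stake is how the result will be read. A non-significant difference would be judged against a stated 80% that has no demonstrated link to the analysis performed.

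**Working it through.** **1. Inputs.** From the Sample size calculation: 30% and 5%, alpha 0.05, power 80%, ratio k = 2 controls per intervention participant. Two-sided testing is assumed, since sidedness is not stated. Then z₀.₉₇₅ = 1.960, z₀.₈₀ = 0.842, and (1.960 + 0.842)² = 7.849.

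**2. Reproducing 30/60 as two proportions.** Take p₁ = 0.30, p₂ = 0.05, difference 0.25. The weighted mean is (0.30 + 2 × 0.05)/3 = 0.1333.

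- Pooled, no correction: n = [1.960·√(1.5 × 0.1333 × 0.8667) + 0.842·√(0.30 × 0.70 + 0.05 × 0.95/2)]² / 0.25² = (0.816 + 0.407)²/0.0625 = 23.9, so 24/48.
- Continuity-corrected: n = (23.93/4) × [1 + √(1 + 2 × 3/(23.93 × 2 × 0.25))]² = 29.6, with 59.2 controls, so **30/60**.
- Unpooled variance: n = (0.21 + 0.02375) × 7.849/0.0625 = 29.4, so **30/60**.

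Two standard variants return the stated figures and the uncorrected pooled one does not. A one-sided test gives 20, or 25 with correction.

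**3. What 30/60 delivers for a mean change.** The detectable standardised difference at 80% power is 2.802 × √(1/30 + 1/60) = 0.626 SD (normal), or 0.633 SD (t-test). For the enrolled 34/58 it is 2.802 × √(1/34 + 1/58) = 0.605 SD (normal), or 0.612 SD (t-test).

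**4. Translating 30% against 5%.** If both groups start at the same mean m (assumed), the difference in mean change is (0.30 − 0.05) × m = 0.25m. Power at 30/60 is then 80% only when the SD of change is 0.25m/0.633 = 0.395m. At 34/58 the limit is 0.25m/0.612 = 0.409m.

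**5. Range.** The article gives no baseline mean or SD, so every row and column below is an assumption. Power is from a two-sided t-test at 30/60, with 34/58 in brackets.

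| Baseline mean | Difference | SD of change 4 | SD 5 | SD 6 | SD 7 |
|---|---|---|---|---|---|
| 10 | 2.5 | 0.79 (0.82) | 0.60 (0.63) | 0.45 (0.48) | 0.35 (0.37) |
| 12 | 3.0 | 0.91 (0.93) | 0.76 (0.79) | 0.60 (0.63) | 0.47 (0.50) |
| 16 | 4.0 | 0.99 (1.00) | 0.94 (0.96) | 0.84 (0.86) | 0.71 (0.74) |

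The same design spans 0.35 to 0.99 at 30/60, and nothing in the article says where in that range the study lies.

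**The case against.** **The formula is inferred.** The article names none, and the match depends on the variant. A comparison of mean percentage change with an SD near 40 points would also give about 30/60 (0.25/0.633 = 0.395). This objection stands as a limit on wording: a reader might take the two-proportion origin as established, and the text does not establish it. It remains the likelier reading, because 30% and 5% are the only effect inputs, no estimates of variation were said to exist, and step B names a binomial test.

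**An article condenses.** The list of assumptions has a (1) and no (2), so an SD may sit in the full protocol. That is possible, but it fits poorly with the statement that the literature gives no estimates. The point here is also not that an SD was left out. It is that a stated 80% does not follow from the basis stated for it.

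**Sizing and step B may agree.** If both treat the outcome as a proportion, they are consistent with each other, and the article never expressly claims 80% for the regression. This is right, but it widens the problem: step B shares the mismatch, so correcting the power statement alone would be incomplete.

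**The study may be adequately powered.** This is also right. A reader might infer underpowering, but every mean and SD in the range above is assumed, and several combinations exceed 80%. Nor does the article's silence on losses before M6 show that attrition was ignored.

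**Conclusion.** The concern holds in a limited form. The 80% power is unsupported for the 0–34 count and for the step C regression. The numbers very probably come from treating percentage falls in a count as proportions of participants, and step B's binomial test on percentage variation reflects the same confusion.

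For an unadjusted comparison of mean change, 30/60 has 80% power at 0.633 SD and 34/58 at 0.612 SD. The assumed 25-point difference reaches that at 30/60 only if the SD of change is no more than about 0.395 of the baseline mean. This rests on two-sided 5% testing, equal baseline means and a common SD of change.

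Neither underpowering nor a biased estimate is shown. The size of the intervention group was set by site capacity and enrolment has closed, so this is a correction that should be made rather than a reason to doubt the effect estimate.

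**What to change.** 1. State the formula, test and sidedness behind 30/60.
2. Withdraw 80% as a claim about the count endpoint.
3. Report instead that the enrolled 34/58 give 80% power for about 0.61 SD of change, in an unadjusted comparison before any attrition. Express this in harms using the pooled M0 SD, a stated range of M0–M6 correlations r, and the expected number with M6 data. With equal SDs at both visits, SD of change = SD(M0) × √(2(1 − r)). As illustrative values, r = 0.3, 0.5 and 0.7 give detectable differences of 0.72, 0.61 and 0.47 SD(M0).
4. Replace the step B binomial test with a between-group comparison of mean change in the count, so that sizing, step B and step C address one quantity.

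The cost is rewording and a short calculation on pooled M0 data, with no group comparison and no extra patients. Data collection was still under way according to Trial status, so this can be done before results are examined. The downside is that the restated figure may be less favourable than 80%.

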#### Inclusion criteria

ETHER’s inclusion criteria were as follows: at least 18 years old; able to provide written informed consent; fluent French speaker; reachable by phone; and followed for AUD in one of the four recruitment centres (i.e., the TPE site and the three control group sites). These inclusion criteria were consistent with the eligibility criteria for participation in Choizitaconso. Participants from the inpatient private clinic in Marseille must first complete medically-supervised withdrawal before inclusion. Exclusion criteria were cocaine or opiate dependence, pregnancy, being a legally-protected adult (tutorship, curatorship), already participating or planning to participate in another study during ETHER’s 6-month follow-up period, and having severe cognitive impairment or psychiatric disorders which could hamper an appropriate assessment of the intervention effects in the 6-month interviews.

#### Data analysis plan

The planned data analyses will be organized in several steps as follows:(A)Descriptive analyses: sociodemographic data and alcohol consumption levels will be compared across study sites and between both the intervention and control groups at enrolment, using parametric and non-parametric tests.(B)Comparison between enrolment (M0) and 6 months (M6) of the percentage variation in the number of alcohol-related harms, using a binomial test.(C)Modelling of variation in the number of alcohol-related harms using linear regression, to determine whether any differences between groups persists after adjustment for possible confounders (identified in step A) or other predictors.(D)Repeat analysis B and C for secondary outcomes using linear regression models.(E)Post-study analysis: factor analysis to aggregate the alcohol-related harms measured at enrolment, in order to identify one or two main alcohol-related harm dimensions, and verify to what extent the intervention is effective for these dimensions.

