##### Secondary outcomes

The controlled intervention study’s secondary outcomes are anticipated and internalized stigma (stigma being of high importance as it is associated with care avoidance or delayed care [39]), quantity and frequency of alcohol consumption, craving for alcohol, coping strategies, HRQoL, self-confidence to control or abstain from drinking, treatment self-regulation, anxiety and depressive symptoms, alcohol-related neuropsychological impairments and capabilities. Each is measured at programme initiation and 6 months later. The measurement methods (face-to-face interview and CATI interview) and the questionnaires used are listed in Table 2.

**Table 2 Tab2:** Study outcomes

Collection	Outcomes	Description	Outcome items
CATI interview	Number of alcohol-related harms (primary outcome)	34 physical, social and behavioural alcohol-related harms^1^ (risk taking, accidents, insomnia, etc.)	34 Community-validated items
	Stigma	Anticipated and internalized stigma	“The Substance Use Stigma Mechanism Scale” (SU-SMS) [45]
	Alcohol consumption	Frequency and quantity of alcohol consumption, binge drinking	Short form of the “Alcohol Use Disorder Identification Test” (AUDIT-C) [40]
	Craving	Craving for alcohol (strong desire or compulsion to consume alcohol)	*Community-validated items (for the three previous months)* “Did you picture alcohol or drinking?” “Did you have a strong urge to drink” “What level of control did you have over your alcohol consumption?”
	Coping strategies	Cognitive and behavioural efforts to cope with stress in everyday life (trait coping)	*“Brief COPE”* [46] Coping dimensions: (1) active coping, (2) planning, (3) using instrumental support, (4) using emotional support, (5) venting, (6) behavioural disengagement, (7) self-distraction, (8) self-blame, (9) positive reframing, (10) humour, (11) denial, (12) acceptance, (13) religion, (14) substance use
	Health-related Quality of Life (HRQoL)	Mental and physical health	*“Short-Form 12-item Health Survey (version 2)”* (SF-12v2) [47] 8 domains: physical functioning, role-physical, bodily pain, general health perceptions, vitality, social functioning, role-emotional, mental health
	Self-confidence to abstain from or control drinking	Confidence to abstain from or control drinking in high-risk situations	“Brief Situational Confidence Questionnaire” (BSCQ) [48]

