## Limitations

Our study has limitations. First, assignment to the two study groups (i.e., intervention and control) is not randomised. Nevertheless, specific statistical methodology (selection models) can be applied later, if needed, to control for non-randomization bias. Second, we are using self-reported alcohol use measures, which may be subject to social desirability bias. However, the validity of self-reported alcohol use has been proven in previous research [44], especially when trained interviewers administer the interview in a non-judgmental environment. Lastly, our primary outcome, tailored to our participants, is not yet validated, but we aim to check for its internal consistency during analyses of the results using Cronbach’s alpha.

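### In a non-randomised comparison, step C takes its confounders from baseline tests of sociodemographic and consumption data alone, and leaves out the measures most likely to separate programme joiners from controls

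*Protocol article*

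**What the plan says.** All references are to the protocol article.

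- **Limitations** states that "assignment to the two study groups (i.e., intervention and control) is not randomised". The remedy offered is that "specific statistical methodology (selection models) can be applied later, if needed, to control for non-randomization bias". No model, trigger or timing is given.
- **Data analysis plan, step A** is the descriptive step: "sociodemographic data and alcohol consumption levels will be compared across study sites and between both the intervention and control groups at enrolment". These comparisons are made by significance tests, for which no threshold is stated.
- **Data analysis plan, step C** models the change in the number of harms by linear regression, "to determine whether any differences between groups persists after adjustment for possible confounders (identified in step A) or other predictors". The other predictors are not named.
- **Recruitment and data collection** shows how the intervention group arose: "At the beginning of a programme session, all participants were presented ETHER study and proposed to participate". Controls came from two CSAPAs and an inpatient clinic, the clinic supplying about half.
- **Inclusion criteria** adds: "Participants from the inpatient private clinic in Marseille must first complete medically-supervised withdrawal before inclusion".
- **Secondary outcomes** says of stigma, consumption, craving, coping, HRQoL, confidence, self-regulation, HADS, BEARNI and capabilities: "Each is measured at programme initiation and 6 months later". The M0 harm count is also collected. Apart from consumption, step A names none of these.

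**The concern.** Confounding arises when a variable differs between groups and also predicts the outcome. In this design the groups differ by construction. One consists of people already starting a programme that lets them choose a drinking goal. About half of the other entered after supervised withdrawal in a clinic. The Discussion itself expects the programme to appeal to people unready or unwilling to abstain. Goal, motivation, confidence, craving, mood and cognition are therefore natural candidates for adjustment, as are baseline harm level and care setting. Several are measured at M0, yet the step that supplies the confounders does not list them.

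A secondary weakness is that the variables step A does list are compared by tests. With 34 and 58 participants, a p-value says little about whether an imbalance is large enough to matter.

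At stake is the primary contrast. If variables outside the screen differ between groups and predict change in harms, the step C estimate mixes programme effect with selection. The reader also cannot tell in advance which adjusted estimate will be reported.

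**Working it through.** **The plan's own figure.** The sample size is 30 intervention and 60 control for a 30% versus 5% reduction, alpha 0.05, power 80%. Treating 30% and 5% as proportions of people, two-sided, ratio 1:2, the pooled proportion is (0.30 + 2×0.05)/3 = 0.133. The uncorrected formula gives [1.96×√(0.1156×1.5) + 0.842×√(0.21 + 0.0475/2)]² / 0.25² ≈ 24 in the smaller group. The continuity correction raises this to 30, hence 60 controls. The stated size is reproduced. Nothing below depends on it.

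**Inputs.** From the document: 34 and 58 enrolled. Assumed, because the document gives none of them: a two-sided 5% cut-off for step A, imbalances of 0.3 to 0.5 SD, and correlations of 0.3 to 0.5 between the confounder and change in harms. Change is scaled to SD 1.

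**Detectable effect at 34 versus 58.** SE = √(1/34 + 1/58) = 0.216 SD. The normal approximation at 80% power gives (1.96 + 0.842)×0.216 = 0.605; with the t distribution it is 0.61 SD.

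**What a baseline test detects** (two-sample t-test):

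| True imbalance (SD) | Chance of being flagged |
|---|---|
| 0.2 | 15% |
| 0.3 | 28% |
| 0.4 | 45% |
| 0.5 | 63% |

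**Case 1: a confounder never considered.** Bias = imbalance × correlation.

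- At 0.4 and 0.4: 0.16 SD. Relative to the detectable effect, 0.16/0.61 = 0.26.
- Over the assumed range: 0.3×0.3 = 0.09 SD to 0.5×0.5 = 0.25 SD.
- Type I error = Φ(bias/SE − 1.96) + Φ(−bias/SE − 1.96). This is 7% at 0.09 SD and 21% at 0.25 SD, against a nominal 5%.

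**Case 2: the same confounder is screened, and adjusted for only if its test is significant.** A non-significant test means the observed imbalance is usually smaller than the true one. By simulation at 0.4 and 0.4:

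- The mean observed imbalance when unflagged is about 0.24 SD, so the bias in those trials is about 0.24×0.4 ≈ 0.10 SD.
- Unflagged trials are about 55% of the total, and flagged trials are adjusted with no bias in this model. The average bias is about 0.55×0.10 = 0.055 SD.
- Over the assumed range, type I error is about 5% to 6%.

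**Comparison.** Average bias is about three times larger for a variable left out of the screen than for one inside it (0.16/0.055 ≈ 2.9). What step A covers matters more than its use of tests.

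**The case against.** **An article condenses.** An unseen analysis plan could list covariates and specify the selection model. That stands for the level of detail. It does not remove the point, because the article states where confounders come from and which variables that step compares.

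**Step A is labelled descriptive and states no cut-off.** This also stands. Selection by p-value is the natural reading of confounders being identified there, but the 5% threshold is an assumption.

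**Step C also allows other predictors, and the Abstract refers to adjusting for other correlates and confounders.** So the text does not confine adjustment to the two screened classes, and a reader who infers that goes too far. The accurate statement is that the missing variables may enter but are not committed to.

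**Other safeguards exist.** Modelling change from M0 to M6 removes stable additive differences in harm level, and eligibility for the study was consistent with eligibility for the programme. Covariate adjustment is therefore not the sole protection. Neither safeguard deals with variables that predict how harms change.

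**Further readings the document does not support.**

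- A reader might infer that the other predictors include values measured after enrolment. Nothing says so.
- A reader might infer that selection models will be chosen once results are known. Limitations leaves the timing open; it does not place the choice after the results, and nothing shows that this happened.
- A reader might apply 0.16 SD to an imbalance that step A tests and misses. That figure belongs only to a confounder never considered; the unflagged case is about 0.10 SD.

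**Conclusion.** The point holds in this form: the source of confounders named for step C is too narrow for a non-randomised comparison of programme joiners with partly inpatient controls, and the one method aimed at non-randomisation is optional.

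Under assumed imbalances and correlations of 0.3 to 0.5, an omitted confounder costs 0.09 to 0.25 SD and brings type I error to 7% to 21%. The central case is 0.16 SD, about a quarter of the detectable effect. Test-based selection of a screened variable is a smaller fault, about 0.055 SD on average in the central case.

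These figures are illustrations. The document reports no baseline imbalance and no correlation with change, so residual confounding is likely from the design but not shown, and its direction is unknown.

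**What to change.** Make these changes before M6 outcomes are compared between groups. Trial status says data collection was still under way, while Background says analyses were ongoing, so any comparison already made should be declared.

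1. In step C, replace confounders identified in step A by a short list chosen on subject-matter grounds, using M0 values only and kept whatever step A shows. An example is M0 harm count, age, sex, M0 AUDIT-C, HADS and treatment self-regulation.
2. Keep step A as description, with standardised differences, and extend it to the M0 measures it now omits.
3. Handle care setting by a sensitivity analysis restricted to CSAPA controls. The withdrawal requirement applies only to clinic controls and the programme runs at one site, so a site term alone cannot separate setting from programme.
4. Replace the optional selection models by one prespecified propensity-based estimate on the same covariates, reported whatever its result.

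**Cost.** This is analysis wording; the clinical measures listed are already collected at M0, and the CATI interview collects sociodemographic data. Six covariates use a few degrees of freedom among 92 participants. The weighted estimate will be less precise, and its stability with 34 treated participants should be checked. The restricted analysis is clearly less precise: taking the 30 CSAPA controls given in the recruitment text, 2.80×√(1/34 + 1/30) ≈ 0.70 SD is detectable, against 0.605 SD by the same approximation with all controls. It should be read for consistency of the estimate rather than for significance.
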